## Method

### Research design

The action research design is a systematic and participatory investigation approach based on the pragmatic-interpretative paradigm [65,66]. This design, through cycles or loops, helps to understand problems and formulate actions directed towards problem-solving [67]. The ultimate aim, objectives and orientations are based on discussion and negotiation with the participants. The researcher takes a participatory attitude to achieve real cooperation [67]. The type of action research proposed by Stringer and Genat [67] targets reflexive professional practice aimed at empowering professional groups to defend clients’ interests. Thus the focus is on the professional who defines the problem based on his/her own practice. The change targets professional practice and the solutions emerging from the professionals and target population. In this study, nurses working with preschool children try to determine possible interventions to promote healthy lifestyles among parents of preschool children to prevent increasing overweight.

In the present action research four cycles (loops) are proposed. Each loop meets a study objective and is composed of a reflection phase and an action phase. Each loop will be described in terms of the methodological approach, sampling strategy and data collection and analysis methods. First, however, the research setting is described.

### Research setting

For this study the research team consists of two professors and a doctoral student. Throughout the study, an advisory committee of stakeholders in the region where the study is conducted will contribute at various steps in the study. The committee members will monitor the study and participate in the thinking regarding its objectives. They come from the local health and social services agency, network of daycare centres, CSSS, the municipality and parents.

The intervention area is a region in the province of Quebec, Canada. The population of this region was 43,953 in 2008 and included 6006 children up to 14 years of age [68]. The preschool vaccination clinics reach many families in both urban and rural areas.

### Awareness of overweight in preschoolers (loop 1)

As the starting point for the study, the nurses participating in the study want to know more about overweight in their preschool population. The first step will be to conduct a prevalence survey. This will provide the participating nurses and researchers with a profile of the population served to initiate thinking and discussions of the study issue. Descriptive quantitative data will be collected to document the situation by estimating the prevalence of overweight and describe the known risk factors.

#### Sample (loop 1)

The study population will be composed of preschoolers who came to vaccination clinics in 2010. The probabilistic sample will comprise 288 consecutive children, for a 95% confidence level, a 5% margin of error and a prevalence that could go up to 25%. The 25% estimate will provide sufficient statistical power. The sample will be created with the consent of the nurses working in the vaccination clinics.

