## Anticipated benefits

The results will give an appreciation of the magnitude of the weight problem in a specific region of Québec and the opportunity to evaluate weight in a vaccination clinic, will describe parents’ representation of overweight and healthy lifestyles in preschoolers, will initiate reflection for the professionals involved and will put in place actions designed to equip parents and families of preschool children in order to prevent and reduce the risks of being overweight. Identification by the professionals of strategies to promote healthy lifestyles in families with preschoolers will be derived from evidence-based data from parents and the literature. The professionals involved in this action research will become more aware of the phenomenon and more expect to benefit from a transfer of knowledge. In addition, the nurses will have resources that will help them intervene and make maximum use of meetings with parents of preschool children to address this health problem. The proposed solutions will foster the integration of new interventions into current practice and open the door to future research on these interventions.

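### The loop 1 sample is labelled probabilistic but is a consecutive series of clinic attenders, so its 5-point margin is conditional and the regional conclusion goes beyond the sample

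*Protocol article*

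**What the plan says.** All references are to the protocol article.

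- Sample (loop 1) defines the population: "The study population will be composed of preschoolers who came to vaccination clinics in 2010". It then gives the selection method and the precision in one sentence: "The probabilistic sample will comprise 288 consecutive children, for a 95% confidence level, a 5% margin of error", with "a prevalence that could go up to 25"%. On access to the children it adds: "The sample will be created with the consent of the nurses working in the vaccination clinics".
- Data collection (loop 1) has the student-researcher measure each child at the clinic and write the values on an anonymous questionnaire. The parent may then complete it or not. Ethical considerations makes weighing and measuring subject to parental permission, which is to be sought for every child whatever the apparent weight.
- Study goals and objectives limits objective 1 to preschoolers who attend a vaccination clinic in the region. Awareness of overweight in preschoolers (loop 1) describes the product as a profile of the population the nurses serve.
- Research setting says of coverage only: "The preschool vaccination clinics reach many families in both urban and rural areas". It gives no percentage.
- Anticipated benefits states: "The results will give an appreciation of the magnitude of the weight problem in a specific region of Québec".

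**The concern.** In a probability sample every unit has a known, non-zero chance of selection, and that is what entitles a margin of error to a design-based reading. Here the word probabilistic and the word consecutive stand in the same sentence, and the second contradicts the first. This is not detail left to a fuller document: the article names its selection method and mislabels it.

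The label matters because of the precision statement attached to it. A reader told that the sample is probabilistic, with 95% confidence and a 5-point margin, will take those 5 points as the full uncertainty of the prevalence. On reaching Anticipated benefits, the same reader will take it as the uncertainty of the regional prevalence. Which children came, when the series ran, whether the nurses agreed and whether the parents agreed all lie outside the margin. In a weight survey, refusal could plausibly be related to the outcome.

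**Working it through.** **1. Reproducing the sample size.** Inputs from Sample (loop 1): p = 0.25, margin d = 0.05, 95% confidence (z = 1.96).

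n = z² p(1 − p) / d² = 1.96² × 0.25 × 0.75 / 0.05² = 288.1, against 288 stated.

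The figure is reproduced without a finite-population correction, design effect or allowance for refusal. It is therefore the simple-random-sampling formula.

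**2. The margin that 288 gives.** Margin = 1.96 × √(p(1 − p)/288).

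| Prevalence | Source | Margin (points) |
|---|---|---|
| 25% | planning value, Sample (loop 1) | 5.0 |
| 21.5% | Canada, ages 2–5, Background | 4.7 |
| 13.5% | Quebec, age 4, Background | 3.9 |

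All three describe random error under simple random sampling and nothing else.

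**3. Whether the design supplies simple random sampling.** Setting the sections side by side, a child enters the data only if the following hold:

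- the child attends a clinic;
- the nurses there have agreed;
- the child falls within the consecutive run of 288;
- the parent permits measurement.

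No step is a random draw with a stated probability. The margin can be used only under the assumption that the enrolled children behave like a random sample of 2010 attenders, and the article does not state that assumption.

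**4. What the assumption is worth.** The article gives no figure for selection bias, so this is a scale and not an estimate. Suppose prevalence among measured children differs from that of the target population by b. With SE = √(0.25 × 0.75/288) = 0.0255, the nominal 95% interval covers the target value with probability Φ(1.96 − b/SE) − Φ(−1.96 − b/SE).

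| Assumed b (points) | Actual coverage |
|---|---|
| 0 | 95% |
| 1 | 93% |
| 2 | 88% |
| 3 | 78% |
| 5 | 50% |

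Nothing in the article says which row applies, or in which direction.

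**5. Target of inference.** Objective 1, the loop 1 study population and the introduction to loop 1 all concern attenders. Only Anticipated benefits moves to the region, and the coverage statement in Research setting is too loose to support that step.

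**The case against.** The strongest reply is that, apart from one word, little is at fault.

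- The stated target is clinic attenders, so attendance defines the population and is not an omitted error source. **This stands for objective 1.** It does not stand for the regional sentence in Anticipated benefits.
- For attenders, a consecutive series with high participation can be treated as approximately random, and a binomial interval is then usable. **This stands, provided the assumption is stated and participation is reported.**
- The regional sentence is softly worded and is not a planned analysis. Data analysis promises a percentage, and loop 1 serves to start discussion among nurses. **This stands, and it limits the consequence.** It does not make the label correct.

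A reader might go further and infer three things that the article does not support.

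*That the margin is too small.* With an assumed 20 children per session and an intraclass correlation of 0.01 to 0.02, the design effect 1 + 19 × ICC is 1.19 to 1.38. The margin at 25% becomes 5.5 to 5.9 points. But the population is small. Research setting gives 6006 children up to age 14, about 400 per year of age if evenly spread (6006/15), so about 801 aged 4–5. The finite-population factor is √((800.8 − 288)/(800.8 − 1)) = 0.80, which brings 5.0 down to 4.0. Combined approximately, 4.0 × √1.19 = 4.4 and 4.0 × √1.38 = 4.7, both below 5.

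*That the estimate is off by several points.* One could treat every unsampled child as uncovered and assume that those children differ by 10 points. A perfect random draw of 288 from about 800 also leaves 64% unsampled, so the sampling fraction says nothing about bias. The article offers no basis for a 10-point gap.

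*That rural or later sessions will be missed.* The article does not say in what order sites or sessions are filled.

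**Conclusion.** The point holds for the label, the meaning of the margin and the reach of the conclusion. The sample is a non-probability, consecutive series of attenders. The sample size is arithmetically right and needs no change. The 5 points are a fair planning figure for random error at a prevalence of 25%, on the unstated assumption that enrolled children resemble a random sample of 2010 attenders. They do not account for selection by attendance, recruitment period or refusal, whose size and direction cannot be determined from the article. The regional conclusion goes beyond the population that objective 1 and the loop 1 sample define.

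The contradiction over the label is certain from the text. The practical effect on the prevalence figure is unknown. No later step of the study is tied to a prevalence threshold, so the consequence lies in how the survey result is read and not in a decision rule.

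**What to change.** - In Sample (loop 1), replace the word probabilistic with *consecutive (non-probability)*.
- Add one sentence saying that the 5-point margin is sampling error only, conditional on the enrolled children behaving like a random sample of 2010 attenders.
- In Anticipated benefits, limit the conclusion to participating clinic attenders.
- Keep a simple tally of eligible, approached and refusing children by site, age and sex, and report participation beside the prevalence. Counts without names are enough and fit the anonymous questionnaire.

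The cost is a small amount of logging at each session, a few words of text and a narrower stated conclusion. The sample size stays at 288.

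Random selection of clinic sessions is not required. It would turn a short descriptive survey into a multistage design and would still leave out non-attenders and refusers, so it would not by itself support a regional statement.

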#### Data collection (loop 1)

The variable of interest is childhood overweight (BMI) for which the reference values used will be those developed by Cole et al. [29]. The following variables will be described: the child’s age, sex, health problems and medications, the family’s postal code (socioeconomic level), the parents’ education, and the height and weight (self-declared) of the parent bringing the child to the vaccination clinic. Data will be collected with a self-administered questionnaire developed specifically for the study, which will be cognitively tested with ten parents to ensure the clarity of the questions, visual presentation and time required to complete it. It will be anonymous and a consent form will be given and explained to parents prior to the questionnaire. At the vaccination clinic, the student-researcher will measure the child’s height and weight and enter this information on the questionnaire, together with the age and sex. She will then give the questionnaire to the parent. At this point, the parent can decide to complete the questionnaire or not. It is expected to take five minutes. A subsection of the questionnaire will invite the parent to voluntarily provide contact information to participate in an interview or focus group in the later loops in the study. After completion, the questionnaire will be left at a specified place.

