## Ethical considerations

The study was approved by the research ethics boards of the Centre hospitalier universitaire de Sherbrooke (CHUS) and Université de Sherbrooke and the Centre de Santé et des Services sociaux (CSSS) Rivière-du-Nord/Nord de Mirabel. Parents and nurses will be asked to sign free and informed consent forms before each data collection. Parents and nurses will be able to withdraw from the study at any time without prejudice. Anonymity will be preserved for those parents who do not wish to be contacted again, and no nominative information will be retained. Confidentiality will be safeguarded in the usual way, such as by keeping the data under lock and key for 5 years, with access restricted to the research team.

The main ethical issues in this study relate to stigmatization of the child and culpability of the parent. Preschool children are a vulnerable group. It will not be possible to identify them (the questionnaire in loop 1 does not ask for children’s names), which reduces the risk of being stigmatized. Also, to reduce the risk of stigmatization, we will ask the parents for permission to weigh and measure all the children, regardless of their apparent weight, for the study. The risk of stigmatization arises later in the lives of children who are overweight for a significant period of time. The parents of children of both normal and overweight will be interviewed, which will minimize the culpability aspect potentially related to the subject of the study. Precautions will be taken when formulating the questions for the interview guide used in loop 2. In addition, psychological support for the family will be available if required at the local health centre (a partner in the study). Particular attention will be paid throughout the study so that parents feel competent in their role.

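### The only described record of each child's height and weight is on a questionnaire that the parent may leave uncompleted, so outcomes already measured can be lost, possibly in relation to weight

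*Protocol article*

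**What the plan says.** All references are to the protocol article.

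- **Data collection (loop 1)** fixes the order of events. At the clinic, "the student-researcher will measure the child’s height and weight and enter this information on the questionnaire", along with age and sex. The sheet then goes to the parent, and "At this point, the parent can decide to complete the questionnaire or not". Once completed, it is left at a designated place. Nothing is said about forms the parent does not complete, and no other record of the measurements is described. The form is called anonymous, yet "A subsection of the questionnaire will invite the parent to voluntarily provide contact information" for the later loops.
- **Sample (loop 1)**: "The probabilistic sample will comprise 288 consecutive children", justified by "a 5% margin of error and a prevalence that could go up to 25" per cent, at 95% confidence. It does not say whether 288 counts children measured or usable forms.
- **Data analysis** takes the prevalence estimate from the loop 1 data.
- **Ethical considerations** names stigmatization of the child and culpability of the parent as the main issues. Permission to weigh and measure is sought for every child whatever the apparent weight, consent is signed before each data collection, and withdrawal is allowed at any time. Of the children it says "It will not be possible to identify them", because the form asks for no child's name. It limits anonymity to parents who do not want further contact.

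**The concern.** The outcome variable leaves the researcher's hands before an optional step. A parent who does not want to answer the questions may keep or discard the sheet, and the child's height and weight go with it. The sheet carries no child's name, so a missing one cannot be traced, and no later analysis can recover the measurement.

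Seeking permission for all children guards against selection before the measurement. It does not guard against loss afterwards. That loss need not be neutral. The parent decides just after the child has been weighed, and the article itself treats weight as a sensitive matter. A second route needs no stigma: the section on etiology lists low family income and incomplete maternal schooling as risk factors for overweight, and either could also affect whether a self-administered form is filled in.

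Prevalence is the first specific objective and the main quantitative result, and loop 2 opens by presenting it to the nurses. If loss depends on weight, the estimate is biased and its confidence interval does not show it. If loss is neutral, precision still falls below plan.

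**Working it through.** **Inputs from the article.** Sample 288, 95% confidence, margin 5 points, prevalence up to 25% (Sample, loop 1). Background prevalences 21.5% (Canada, ages 2–5) and 13.5% (Quebec four-year-olds) (Background).

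**Inputs assumed.** The article gives no return rates. Those below are illustrations only.

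**1. The plan's own figure.**

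n = z² p(1 − p) / d² = 1.96² × 0.25 × 0.75 / 0.05² = 288.1

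The 288 reproduces. It is the number of analysable children required, with nothing added for lost forms.

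**2. Loss unrelated to weight.** If 288 are measured and 80% of forms come back, n = 0.80 × 288 = 230, and the margin at 25% is

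1.96 × √(0.25 × 0.75 / 230) = 0.056, or 5.6 points instead of 5.0.

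There is no bias in this case.

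**3. Loss related to weight.** With true prevalence P and return rates r₁ (overweight) and r₀ (not overweight), the expected estimate is

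P r₁ / [P r₁ + (1 − P) r₀]

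For P = 0.25, r₀ = 0.90, r₁ = 0.70: 0.175 / (0.175 + 0.675) = 0.206, a bias of −4.4 points.

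| True P | 90% vs 80% (not overweight vs overweight) | Bias | 90% vs 70% | Bias |
|---|---|---|---|---|
| 13.5% | 12.2% | −1.3 | 10.8% | −2.7 |
| 21.5% | 19.6% | −1.9 | 17.6% | −3.9 |
| 25% | 22.9% | −2.1 | 20.6% | −4.4 |

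The sign follows from the assumption. If parents of overweight children returned more forms (80% vs 90%), a true 25% would give 0.225 / (0.225 + 0.600) = 27.3%, a bias of +2.3 points.

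**4. Recruiting on to 288 returned forms.** This restores precision but leaves the bias untouched. At P = 25% and 90% vs 70% return, the nominal 95% interval covers the truth about 62% of the time with the 245 forms expected from 288 children, and about 54% of the time with 288 returned forms.

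**5. Bounds without any assumption on direction.** For an observed 25% at overall return R, the prevalence among all children measured lies between 0.25R and 0.25R + (1 − R). At R = 90% this is 22.5% to 32.5%; at R = 80%, 20% to 40%.

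**The case against.** The strongest reply is textual. The article says the parent may choose not to *complete* the form, not that the parent may choose not to *return* it. The measurements are already on the sheet, so a form left blank by the parent still holds the outcome if someone collects it. The article does not say that such forms are discarded, nor that no other log is kept, and a condensed article may leave form handling to the full protocol. This stands as a limit on the claim: loss is possible under the described procedure, not certain. It does not remove the point, because the sequence is stated, and the only return route described applies after completion.

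A reader might also infer that parents of heavier children will hold back forms and that prevalence will be understated. The documents do not support that. Nothing says parents are told the BMI or weight category before they decide. The article's own Table 1 reports that between 32.1% and 98.1% of parents of overweight children did not see them as overweight, which weakens the stigma route. Weight-sensitive refusal could also occur earlier, when permission to measure is sought, and the remedy below does not reach that.

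The survey's stated purpose is a population profile to start discussion. No hypothesis test or decision threshold depends on it, loops 2 to 4 are qualitative, and loop 2 requires a completed questionnaire anyway. A shift of a few points would be unlikely to change what follows. This rightly lowers the severity.

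Finally, a reader might conclude that the anonymity promise is simply untrue for parents who volunteer contact details. Ethical considerations already restricts anonymity to parents who do not wish to be contacted again, and explains the statement about identification by the absence of children's names. What remains is loose wording in the data collection section.

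**Conclusion.** The point holds as a weakness in a stated procedure. As described, outcomes of children measured with permission can be lost after measurement, and the loss could depend on weight, education or income. Its size and direction are unknown. The biases of −1.3 to −2.1 points (90% vs 80%) and −2.7 to −4.4 points (90% vs 70%) rest wholly on assumed return rates and on the assumption that overweight children's forms come back less often. The smaller range is well inside the planned 5-point margin; the upper end of the larger range approaches it. The 5.6-point margin applies only if 288 means children measured and 80% of forms return.

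The sample-size calculation is not wrong; it simply has no room for loss. Given the survey's role as a profile, this is a cheap and worthwhile improvement, not a flaw that undermines the study. It should be made before collection, because a lost measurement cannot be recovered. The anonymity wording is a secondary inconsistency and has no bearing on the bias.

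**What to change.** 1. Before handing over the questionnaire, record age, sex, height and weight on a numbered, nameless sheet that the researcher keeps. Put the same number on the questionnaire.
2. Estimate prevalence on all children measured with parental consent, whether or not the questionnaire is completed, except where the parent withdraws.
3. Report how many children were measured and how many forms were returned, and compare overweight between returners and non-returners.
4. State that 288 refers to children with usable measurements.
5. Align the unqualified description of the questionnaire as anonymous in Data collection (loop 1) with Ethical considerations, which limits anonymity to parents who do not wish to be contacted again.

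The cost is one extra sheet, a numbering scheme and a change to the consent form. That change needs care: declining a nameless form may be the practical way for a parent to withdraw. The consent must therefore say plainly that the measurement is kept even if the questionnaire is not completed, and how a parent can withdraw it. No extra participants or measurements are needed.
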